
## Participant timeline {13}

**Table Tabb:** 

	**STUDY PERIOD**									
	**Enrolment**	**Allocation**	**Post-allocation**							
**TIMEPOINT**	**Preoperative**	**Postoperative**	**3 months**	**6 months**	**9 months**	**12 months**	**15 months**	**18 months**	**21 months**	**24 months**
PACAP or PACOPS registry, TwiCs & PROMs informed consent	X									
Clinical evaluation	X		X	X	X	X	X	X	X	X
Histological evaluation (confirmation PDAC and R0-R1 resection)		X								
Informed consent for study-related surveillance (investigational arm)		X								
Labs: CA 19–9, extra blood sample	X		X	X	X	X	X	X	X	X
CT chest and abdomen	X		X	X	X	X	X	X	X	X
QoL questionnaires^a^	X		X	X	X	X		X		X

^a^The following questionnaires are used: non-disease specific HRQL (EQ-5D-5L), cancer-specific HRQL (EORTC QLQ-C30), tumor-specific HRQL (EORTC QLQ-PAN26), hospital anxiety and depression scale (HADS), worry of progression of cancer scale (WOPS; modified Dutch seven-item version of the six-item english cancer worry scale (CWS))

### Sample size {14}

A retrospective study by Elmi et al. demonstrated that the median overall survival after primary tumor resection was 30.4 months in 163 patients who received routine imaging surveillance, as compared with 17.1 months in 66 patients receiving clinical follow-up without imaging [32]. Data from 1580 patients who underwent PDAC resection between 2014 and 2019 within the Netherlands showed a median overall survival of 33.6 months (95% confidence interval (CI) 29.4–38.2 months) in 284 patients who received routine follow-up imaging and 20.8 months (95% CI 19.8–22.6 months) in 1296 patients undergoing a symptomatic follow-up approach without routine imaging (Fig. 2). Combining these outcomes results in an expected median survival of 32.0 months vs. 19.0 months for patients in the intervention and control arm of the RADAR-PANC trial, respectively.

**Fig. 2 Fig2:**
[figure not shown]
Kaplan–Meier curve comparing overall survival between patients with routine follow-up imaging and symptomatic follow-up in the Netherlands between 2014–2019 (unpublished data)

As we expect 80% of patients to accept the experimental intervention offered in the intervention arm of the study, an estimated refusal rate of 20% needs to be taken into account. This leads to a decrease of the overall survival to 29.4 months (80% × 32.0 months + 20% × 19.0 months) for patients in the intervention arm. Moreover, despite that current non-standardized follow-up in daily clinical practice mainly results in a symptomatic follow-up approach without routine imaging, data from our recurrence database showed that 85/1580 patients (5%) did nonetheless receive routine follow-up imaging based on shared-decision making (the remaining 199/284 patients (70%) who received routine follow-up imaging participated in a clinical study with a study-specific follow-up including routine imaging). This results in a slight increase of the suspected overall survival in the control arm to 19.7 months (95% × 19.0 months + 5% × 32.0 months). The clinically relevant survival difference of 29.4 months vs. 19.7 months for the intervention and control arm, respectively, also approximates the mean survival difference of 9.5 months presented in the meta-analysis from Halle-Smith et al. [33]. These numbers correspond to a relative hazard (RH) of survival of 1.49, which is used to calculate the sample size of the study. Furthermore, as we expect a minimal level of loss to follow-up in this surveillance study, a censoring rate of 1% is expected each month.

To detect a 49% overall survival improvement (RH of survival 1.49) for patients in the intervention group, as compared with the control group, with a statistical power of 80% and a 0.05 two-sided significance level, a sample size of 306 patients is required. This calculation was based on the assumption of an exponential model, a median overall survival of 19.7 months in the control arm, a follow-up duration of 30 months, a drop-out rate of 1% and a baseline event rate of 3.5%. Following this calculation, we plan to include 306 patients in total: 153 patients in the recurrence-focused follow-up group and 153 patients in the non-standardized, symptomatic follow-up group.

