### Statistical methods

#### Statistical methods for primary and secondary outcomes {20a}

The latest version of R Studio will be used for statistical analysis.

Baseline characteristics will be reported using standard descriptive statistics. Success of randomization will be evaluated by eye-balling whether the distribution of baseline characteristics between the intervention and control group is even. Primary analysis will be performed according to the intention-to-treat principle. As such, patients randomized to the intervention arm of the trial who refuse recurrence-focused surveillance following the TwiCs design will be analyzed as part of the intervention group. The main study parameter is overall survival, measured as the time from the date of PDAC resection to the date of death. Patients are censored at the time of last known follow-up visit documented if no event occurred. Overall survival rates will be reported as median with 95% CI and will be calculated by the Kaplan–Meier survival curve method. Log-rank test will be used to compare survival between the intervention and control group. One- and 2-year survival probabilities will be calculated. Univariate Cox-proportional hazard analysis will be used to assess the crude effect of a recurrence-focused surveillance strategy on survival. In addition, adjusted effect estimates will be calculated using a multivariable Cox-proportional hazard model, including potential confounders for symptomatic PDAC recurrence. To address potential confounders for which the multivariable analysis needs to be adjusted, a Directed Acyclic Graph was designed on https://www.dagitty.net (Fig. 3). It is hypothesized that a recurrence-focused postoperative surveillance strategy leads to the detection of PDAC recurrence in an asymptomatic stage, which increases the probability to undergo treatment for recurrence, possibly improving survival. The association between postoperative surveillance strategy and overall survival is therefore fully mediated through presence of symptoms at the time of recurrence diagnosis and subsequent administration of recurrence treatment. Given that the median overall survival after resection of PDAC is 21 months and 1- and 2-year survival rates are 75% and < 50%, respectively, we expect that during our follow-up period at least 50% of included patients (*n* = 153) will experience an event. The number of variables included in the multivariable analysis is based on the rule of thumb of ~ 10 events per variable, where a categorical variable counts for the number of categories. Consequently, multivariable analysis is adjusted for 15 baseline covariates that are considered to be the most important, i.e., age (continuous), sex (male/female), and predictors that reflect an (un)favorable tumor biology or treatment course, including performance status (continuous), preoperative CA 19–9 value (continuous), tumor location (head/distal), resection margin status (R0/R1), tumor size (continuous), number of positive lymph nodes (continuous) and tumor differentiation (poor/well-moderate), and administration of adjuvant therapy (yes/no). Given that recurrence treatment is considered a mediator, and not a confounder, no adjustment for recurrence treatment is required. Because administration of neoadjuvant therapy is known to affect preoperative CA 19–9 values, resection margin status, tumor size, and number of positive lymph nodes, neoadjuvant treatment will not be adjusted for. Postoperative complications are deemed to affect the receipt of adjuvant therapy and will thus not be included in multivariable analysis. Results will be presented as hazard ratio’s (HR) with corresponding 95% confidence intervals (CI). A two-tailed *P-*value < 0.05 will be considered statistically significant.

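### The planning relative hazard of 1.49 rests on weighted means of medians; the stated exponential model gives about 1.47, and the power of 306 patients should be restated with the intervention hazard reduced

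*Protocol article*

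**What the plan says.** All references are to the protocol article. Sample size {14} combines a retrospective study with Dutch national data: "Combining these outcomes results in an expected median survival of 32.0 months vs. 19.0 months". The text under Fig. 2 then dilutes both medians:

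- Intervention arm: "an estimated refusal rate of 20% needs to be taken into account", so the median becomes "80% × 32.0 months + 20% × 19.0 months" = 29.4 months.
- Control arm: "85/1580 patients (5%) did nonetheless receive routine follow-up imaging", so the median becomes "95% × 19.0 months + 5% × 32.0 months", stated as 19.7 months.

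The pair 29.4 and 19.7 is converted to a relative hazard of 1.49. The section states that 306 patients (153 per arm) give 80% power at two-sided 0.05. Its other assumptions are an exponential model, a control median of 19.7 months, 30 months of follow-up, 1% censoring per month and a baseline event rate of 3.5%. Recruitment {15} adds 28 months of accrual and a final analysis 30 months after the last patient enters. The section on non-adherence {20c} relies on this step when it says that the sample size is corrected for refusal and for routine imaging among controls.

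**The concern.** Dilution acts on survival curves. The survival function of a mixed group is the weighted average of the subgroup survival functions, and its median is the time at which that average reaches one half. For exponential subgroups this time lies below the weighted mean of the medians. Both diluted medians are therefore too high. The intervention median is affected more, because its mixture is more even, so the ratio is too large.

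The relative hazard is the single effect figure behind 306 patients and 80% power. If it is too large, a null result will be read against more power than the planning assumptions give. Any restatement must also fix the number of deaths, and here the stated 306 has a second difficulty, shown below.

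**Working it through.** **Inputs.** Undiluted medians 32.0 and 19.0 months; refusal 20%; control imaging 5%; control median 19.7; 30 months of follow-up; censoring 1% per month; 1:1 allocation; 28 months of accrual. All are from Sample size {14} and Recruitment {15}. Assumptions added here: refusers have the 19.0-month median, each subgroup is exponential, and accrual is uniform.

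**1. The plan's effect figure.** 0.80 × 32.0 + 0.20 × 19.0 = 29.4. 0.95 × 19.0 + 0.05 × 32.0 = 19.65, stated as 19.7. 29.4 / 19.7 = 1.49.

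**2. Mixture medians.** Solve p·2^(−t/32) + (1 − p)·2^(−t/19) = 0.5.

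- p = 0.80: t = 28.69. Check: 0.80 × 0.5372 + 0.20 × 0.3512 = 0.500.
- p = 0.05: t = 19.45. Check: 0.05 × 0.6561 + 0.95 × 0.4918 = 0.500.

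The ratio is 28.69 / 19.45 = 1.475. The mixture hazards are not exactly proportional; the average that the log-rank test sees over 30 months is about 1.469. Either way, about 1.47.

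**3. Deaths needed.** Schoenfeld: 4(1.96 + 0.84)² / (ln RH)², where the squared sum is 7.849 unrounded.

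- RH 1.49: 197
- RH 1.475: 208
- RH 1.469: 212

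**4. Reproducing 306.** The probability of an observed death by 30 months is λ/(λ + c) × [1 − exp(−30(λ + c))], with c = 0.01 and control λ = ln 2 / 19.7 = 0.0352. For controls this is 0.578.

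- Intervention hazard **raised** (0.0352 × 1.49 = 0.0524): 0.711. Mean 0.644. 197.4 / 0.6443 = 306.4, which is the stated figure.
- Intervention hazard **reduced** (0.0352 / 1.49 = 0.0236): 0.446. Mean 0.512. 197.4 / 0.5121 = 385.5. Here 306 patients give about 157 deaths, and power is Φ(√156.7 × ln 1.49 / 2 − 1.96) = 70%.

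Other variants in the intended direction (Freedman's formula, no drop-out, staggered entry with and without drop-out) did not come within 3% of 306.

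**5. The averaging error in isolation.** Keep the calculation that yields 306 and change only the dilution. Power goes from 80% to 78.0% (RH 1.475) or 77.2% (RH 1.469), and the number for 80% power goes to 322–328.

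**6. Power of 306 patients, hazard reduced.**

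| Follow-up and censoring | Deaths (RH 1.49 / mixture) | Power at RH 1.49 | Power with mixture |
|---|---|---|---|
| 30 months each, 1% per month | 157 / 158–159 | 70% | 68–69% |
| 28-month accrual + 30 months, 1% per month | 184 / 186 | 77% | about 75% |
| 28-month accrual + 30 months, none | 217 / 219 | about 84% | 81–82% |

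**7. Sensitivity to the starting medians.** The 32.0 and 19.0 agree with simple means of the two sources: (30.4 + 33.6)/2 = 32.0 and (17.1 + 20.8)/2 = 18.95. The national data alone (33.6 and 20.8) give mixture medians of 30.4 and 21.3 and a ratio of 1.43. In the three settings of the table, power is then about 59%, 67% and 74%.

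**The case against.** The strongest reply is that the averaging error is minor. It moves the relative hazard from 1.49 to 1.47 and power by 2–3 points. The corrected difference, 28.7 − 19.5 = 9.2 months, is about as close to the 9.5 months that the article cites from a meta-analysis as its own 9.7 is. This stands, and the point is sized accordingly. It is also true that power to detect 1.49 is conditional on 1.49. How that figure was derived bears on whether it is the effect to expect, and does not by itself falsify power at that value.

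Three stronger readings are tempting, and the documents do not support them.

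- A reader might infer that averaging medians is the main reason why 80% is too high. It is not. Most of the shortfall in the first row of the table comes from the direction of the hazard in the event count.
- A reader might see a contradiction between 19.0 months and the statement in {20a} that "the median overall survival after resection of PDAC is 21 months". That figure covers all resected patients, including those with routine imaging, so a value above 19.0 is expected.
- A reader might re-weight the two sources by patient numbers and report a much lower power as an error. Equal weighting is a planning judgement, and a patient-weighted figure would again be a weighted mean of medians. The 19.0 months does lie below the national 95% CI of 19.8–22.6. However, equal weighting also lowered the intervention median from 33.6 to 32.0, which works against the trial. This justifies a sensitivity line only.

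Finally, 306 patients may still reach 80% power. With staggered entry and no censoring they do, so a flat statement that the trial is underpowered would go too far.

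**Conclusion.** The diluted medians and the relative hazard are wrong as written: about 28.7, 19.5 and 1.47 under the stated model, against 29.4, 19.7 and 1.49. In isolation this is a small overstatement, with 208–212 deaths needed instead of 197 and 77–78% power instead of 80%.

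The 77–78% should not be entered as the trial's power, because it keeps an event count that arises only when surveillance raises the hazard. With the hazard reduced, power is about 68–69%, 75% or 81–82%, depending on whether accrual time is counted and whether censoring occurs. The article itself assumes 1% monthly censoring, which points to the first two. In line with this, {20a} expects at least 153 deaths. That is a floor and not a target, but it is close to the 157 of the intended direction.

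The result rests on exponential subgroups, refusers having the 19.0-month median, and uniform accrual. That the hazard was entered in the wrong direction is inferred from what reproduces 306; the article does not show the step.

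**What to change.** In Sample size {14}:

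- Replace 29.4, 19.7 and 1.49 by 28.7, 19.5 and about 1.47, obtained from S_I(t) = 0.80·S(t; 32.0) + 0.20·S(t; 19.0) and S_C(t) = 0.95·S(t; 19.0) + 0.05·S(t; 32.0). The improvement of 49% becomes about 47%, and the baseline event rate becomes ln 2 / 19.45 = 3.6% per month.
- Restate the power of 306 patients from the deaths expected with the intervention hazard reduced. Say whether the 28-month accrual is counted and what censoring is assumed. Giving all three rows of the table would be clearest.
- Optionally add one sensitivity line with the national medians (33.6 and 20.8, mixture ratio about 1.43), labelled as an alternative planning assumption.

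This is a change of text only, with no change in enrolment. The cost is that the stated power becomes less favourable under the article's own censoring assumption.

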### Provisions for post-trial care {30}

Individual patients will remain enrolled in the RADAR-PANC trial for a maximum of 2 years or until patient withdrawal. Follow-up of patients that have completed the 2-year follow-up will be continued for survival information until death. Patients who are withdrawn from the study will be followed-up by a medical specialist or general practitioner for survival information until death. After the study period has ended for an individual patient, continuation of either recurrence-focused or non-standardized follow-up and diagnostic testing is based on shared decision-making between patients and their treating physicians.

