### Recruitment {15}

To achieve adequate patient enrolment and reach the target sample size, all centers are encouraged to participate in the current trial. To ensure enrolment of all eligible patients, the study coordinator(s) are in close contact with the local investigators at the participating centers to obtain weekly updates about patients who underwent macroscopically radical PDAC resection. Eligible patients will be contacted by the study coordinators in consultation with the treating clinicians. If an eligible patient is not yet approached for participation in the PACAP or PACOPS project, informed consent for PACAP or PACOPS, including TwiCs and PROMs, will be discussed by the study coordinator(s).

In 2018, 2348 patients were diagnosed with pancreatic cancer in the Netherlands. About 20% (*n* = 470) of these patients underwent macroscopically radical (R0-R1) resection of the tumor. In the Netherlands, all pancreatic resections are performed in centers affiliated with the DPCG, which will all participate in the current study. Based on the current successful enrolment progress, we anticipate that 75% (*n* = 353) of all patients will be registered yearly in the PACAP cohort and that 80% (*n* = 282) of these patients will provide informed consent for the TwiCs design. About 150 patients each year are expected to be included in other studies with a study-specific follow-up, which is an exclusion criterium for the RADAR-PANC trial. This leaves 282 – 150 = 132 patients eligible for randomization in the current study each year. Fifty percent (*n* = 66) of patients will be randomized to a standardized surveillance strategy. We expect that 80% (*n* = 53) of these patients are willing to participate in the intervention arm of the study, with a participation rate of 100% (*n* = 66) in the control arm as a consequence of the TwiCs design. The expected time needed for inclusion of a total of 306 patients (153 patients in each arm) is therefore 28 months. The final analysis will be performed 30 months after the last patient is enrolled.

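### The 306 patients stated for 80% power do not follow from the sample-size inputs in the hypothesised direction; power is about 70% on those inputs and 77–78% under the calendar rule with the stated 1% monthly loss

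*Protocol article*

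**What the plan says.** Sample size {14} starts from "The clinically relevant survival difference of 29.4 months vs. 19.7 months for the intervention and control arm, respectively", and turns the ratio of these medians into a relative hazard of 1.49. The direction is explicit: "To detect a 49% overall survival improvement (RH of survival 1.49) for patients in the intervention group, as compared with the control group". The conclusion is that "with a statistical power of 80% and a 0.05 two-sided significance level, a sample size of 306 patients is required", split 153 and 153.

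The inputs are listed in the same section. "This calculation was based on the assumption of an exponential model, a median overall survival of 19.7 months in the control arm", with "a follow-up duration of 30 months, a drop-out rate of 1% and a baseline event rate of 3.5" per cent. The sentence before it makes clear that the 1% censoring is per month. The 3.5% is also monthly, since ln 2 / 19.7 = 0.0352. No accrual period is among these inputs.

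Recruitment {15} expects inclusion to take 28 months and sets the time of analysis: "The final analysis will be performed 30 months after the last patient is enrolled". Trial status gives a first enrolment in March 2021 and expects recruitment to end in April 2024, about 37 months. Provisions for post-trial care {30} adds: "Follow-up of patients that have completed the 2-year follow-up will be continued for survival information until death".

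**The concern.** A lower hazard in the intervention arm means fewer deaths per patient and so more patients for the same number of deaths. A total of 306 looked too small for a control median of 19.7 months, an intervention median of 29.4 months, 30 months of follow-up and 1% monthly loss.

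Overall survival is the only primary endpoint, no interim analysis is planned, and the final analysis is set by the calendar. If the deaths fall short, no other rule in the article restores the information. At 70% power the chance of missing the hypothesised effect is 30%, and at 77% it is 23%, against the stated 20%.

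**Working it through.** **Inputs** (Sample size {14}): two-sided 0.05, so z = 1.960; power 80%, so z = 0.842; RH = 1.49, so ln RH = 0.3988; control hazard λ0 = ln 2 / 19.7 = 0.03519 per month; censoring c = 0.01 per month; follow-up F = 30 months; 1:1 allocation.

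**Deaths needed** (Schoenfeld): 4 × (1.960 + 0.842)² / 0.3988² = 197.4, so 198.

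**Probability of an observed death**, with F months for every patient: p = λ/(λ + c) × [1 − exp(−(λ + c)F)]. Control arm: 0.578.

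**Reproducing 306.** Multiply the control hazard by 1.49: λ1 = 0.0524 per month, a median of 13.2 months. Then p1 = 0.711, the mean of the two arms is 0.644, and N = 197.4 / 0.644 = 306.4. Using the rounded 3.5% gives 307.2.

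**Hypothesised direction.** Divide instead: λ1 = 0.03519 / 1.49 = 0.0236 per month, a median of 29.4 months. Then p1 = 0.446, the mean is 0.512, and N = 385.5 (386.8 with the rounded 3.5%). With 306 patients, the expected deaths are 306 × 0.512 = 156.7. Power = Φ(√156.7 / 2 × 0.3988 − 1.960) = 70.4%. A log-rank simulation of 10,000 trials gave 71.3%.

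**Crediting Recruitment {15}.** For uniform accrual over A months and analysis F = 30 months after the last patient, with s = λ + c: p = λ/s × [1 − (exp(−sF) − exp(−s(F + A)))/(sA)]. With A = 28 and 1% loss, p = 0.665 (control) and 0.536 (intervention).

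All rows below use the hypothesised direction:

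| Follow-up | Loss per month | Deaths from 306 | Power | N for 80% |
|---|---|---|---|---|
| 30 months each | 1% | 156.7 | 70.4% | 385.5 |
| 30 months each | none | 177.4 | 75.7% | 340.5 |
| 28-month accrual + 30 | 1% | 183.8 | 77.1% | 328.7 |
| 28-month accrual + 30 | 0.5% | 199.3 | 80.4% | 303.1 |
| 28-month accrual + 30 | none | 217.0 | 83.6% | 278.4 |
| 37-month accrual + 30 | 1% | 189.3 | 78.3% | 319.2 |
| 37-month accrual + 30 | 0.5% | 206.3 | 81.7% | 292.8 |
| 37-month accrual + 30 | none | 226.0 | 85.0% | 267.3 |

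The simulation for 28-month accrual with 1% loss gave 77.4%.

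**When 198 deaths would occur.** Solving 306 × mean p = 198 for F at 1% loss gives 40.6 months after the last patient (28-month accrual) or 37.0 months (37-month accrual). At 0.5% loss the answers are 29.4 and 25.7 months, both before the planned analysis.

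**The case against.** The strongest reply is that 70% is not the power of the trial as it will be run. Thirty months is the minimum follow-up under Recruitment {15}, early patients contribute up to 28 + 30 = 58 months, and survival is followed until death. This stands: the practical shortfall at 1% loss is then 2 to 3 points, not 10. A reader might infer that the trial is 386 − 306 = 80 patients short. The documents do not support that for the calendar design, which needs about 319 to 329.

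The remaining gap also depends on the loss rate. The article itself calls the expected loss minimal and follows ill and withdrawn patients through their doctors. At 0.5% per month the calendar design passes 80%. But 1% per month is the figure the protocol states, and at that figure neither reading of follow-up reaches 80%.

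A reader might also take the reversed direction as established. It is not, because the calculation is not shown. A one-sided 0.05 test in the hypothesised direction comes close: 4 × (1.645 + 0.842)² / 0.3988² = 155.5 deaths, and 155.5 / 0.512 gives N = 303.7. That contradicts the stated two-sided level and fits less well than 306.4, but it cannot be excluded. Two-sided power with 306 patients is 70% whichever slip occurred.

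Finally, Statistical methods {20a} expects deaths in "at least 50% of included patients", that is 153, which might be read as a planned total that contradicts 198. It is a floor, used to count how many covariates the Cox model can carry. A floor of 153 does not conflict with a requirement of 198.

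**Conclusion.** The sample-size statement is wrong as written: 306 patients, 80% power and two-sided 0.05 do not fit together under the listed inputs and the hypothesised benefit. Power is about 70% with 30 months per patient, and about 77–78% when accrual and the time of analysis are credited, both at 1% monthly loss. Both figures should be given, because 70% alone overstates the practical shortfall.

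The result rests on exponential survival, proportional hazards, uniform accrual for the calendar figures, and equal loss in both arms. A hazard multiplied instead of divided is the likely cause, and the conclusion does not depend on it. A calendar-timed final analysis is a legitimate choice and not itself an error.

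**What to change.** Redo the calculation with an intervention hazard of 0.0352 / 1.49 = 0.0236 per month. State the 198 deaths needed, and restate the power of 306 patients as about 70% on the inputs in Sample size {14} and about 77–78% under the rule in Recruitment {15} with 1% monthly loss. Say which of the two describes the planned analysis, and name the accrual period among the inputs. This costs amendment wording only.

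Optionally, time the final analysis at 198 deaths and not earlier than 30 months after the last patient. Survival is already followed until death, so no patients or study visits are added. The downside is delay: at 1% monthly loss the analysis would fall about 37 to 41 months after the last patient instead of 30, that is 7 to 11 months later. At about 0.5% or less there is no delay. Because the loss rate is uncertain, a latest calendar date should be fixed with the rule.
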